## 10. Study Plan

### 10.1. Overall Design and Plan of the Study

This clinical study was designed as a dose blocked-randomized, double-blind, placebo-controlled, single and multiple dosing, dose-escalation phase I clinical trial.

- 1) Single ascending dose study (30 mg, 60 mg, 240 mg, 480 mg, 960 mg)

[figure not shown]

Volunteers for this study are selected as subjects if they are judged eligible for this study by undergoing screening procedures such as history taking, physical examinations, and clinical laboratory tests within 4 weeks (-28 ~ -2d) before the first administration.

Subjects are randomized after admission to the Clinical Trials Center, Seoul National University Hospital in the afternoon of the day of admission (-1d), and have dinner around 6 PM. On the dosing day (1d), the investigational drug is orally administered with 150mL of water at around 9 AM (reference time, 1d 0h), and food including drinking water is prohibited from 1 hour before administration to 4 hours after administration. Thereafter, the subjects conduct the study according to the predefined schedule and discharge at 4d. After discharge, subjects visit the Clinical Trials Center on the morning of 5d, 6d, and 7d to perform the scheduled procedures.

The subjects who complete whole study conduct the Post Study Visit(PSV) between 12d and 16d at their convenience.

- 2) Single dose study (120 mg, Food effect study)

[figure not shown]

Volunteers for this study are selected as subjects if they are judged eligible for this study by undergoing screening procedures such as history taking, physical examinations, and laboratory tests within 4 weeks (-28 ~ -2d) before the first administration.

Subjects are randomized after admission to the Clinical Trials Center, Seoul National University Hospital in the afternoon of the day of admission (phase 1 -1d), and have dinner around 6 PM. On the dosing day of the first period (phase1 1d), the investigational drug is orally administered with 150mL of water at around 9 AM (reference time, phase 1d 0h), and food including drinking water is prohibited from 1 hour before administration to 4 hours after administration. Thereafter, the subjects conduct the study according to the predefined schedule and discharge at 4d. After discharge, subjects visit the Clinical Trials Center on the morning of 5d, 6d, and 7d to perform the scheduled procedures.

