The 2nd dosing is planned with an at least 14 days after 1st dosing. The subject is admitted to the Clinical Trials Center, Seoul National University Hospital in the afternoon of the 2nd period admission day (phase 2 1d) and has dinner around 6 PM. On the dosing day of the second period (phase 2 1d), subjects start a high-fat meal (more than 900 kcal, more than 35% fat) 30 minutes before administration of the investigational drug and complete it within 20 minutes, and the investigational drugs are orally administered with 150mL of water at around 9 AM (reference time, phase1 1d 0h). Food including drinking water is prohibited from 1 hour before administration to 4 hours after administration. Thereafter, the subjects conduct the study according to the predefined schedule and discharge at 4d. After discharge, subjects visit the Clinical Trials Center on the morning of 5d, 6d, and 7d to perform the scheduled procedures.

The subjects who complete the whole study conduct the Post Study Visit(PSV) between 12d and 19d from the phase2 dosing date at their convenience.

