#### 10.5. Dose Escalation to the Next Dose Level

When safety data up to the the last pharmacokinetic sampling day of the all subjects for each dose group are available, the next dose level can proceed if it is determined that safety and tolerability have been adequately demonstrated through the review of the internal safety review committee (SRC) composed of the Investigators and the Sponsor. The elderly dose group(120 mg) of the multiple dose study proceeds after the maximum tolerated dose (MTD) group or the 480 mg dose group is completed. When proceeding from a single dose study to a multiple dose study, and when determining the administration dose in the elderly dose group within the multiple dose study, the appropriate administration dose is determined after review by the Safety Review Committee (SRC) including independent experts. The SRC is made up of the investigators, the sponsor, and cardiovascular or neurological experts.

When determining whether safety and tolerability have been adequately demonstrated, the Principal Investigator remains blind to the treatment group (test group or placebo group). However, when the treatment information is critical to the subject safety and/or dose escalation decision, the Principal Investigator could be unblinded.

Considering the drug's half-life after administration and study schedule in the single and multiple ascending dose study, safety and tolerability is evaluated within the last pharmacokinetic sampling day of all subjects in the dose group. If it is judged acceptable through the internal SRC review, proceed to the next dose level after discussion and the investigator's judgment has priority for adverse events occurring within the period.

After evaluating the severity of adverse events(safety test results(including clinical laboratory tests, vital signs, etc.) and adverse reactions of all subjects who administered the investigational drug) based on the Common

Terminology Criteria for Adverse Events (CTCAE) version 5.0 or the latest version, the Principal Investigator can decide whether or not to discontinue the entire study. In addition, if the following occurs, the dose escalation can be stopped through discussion between the investigator and the sponsor.

- When a Grade 3 or higher adverse drug reaction occurs in more than 1/4 of the subjects
- When a Grade 4 or higher adverse drug reaction occurs in one or more subjects

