#### 12.1.2. Safety/Tolerability Analysis

All AEs are classified using the MedDRA (Medical Dictionary for Regulatory Activities). Summarize the number of subjects (occurrence rate) and the number of occurrences of adverse events/adverse drug reactions and serious adverse events/adverse drug reactions by dose group and treatment group. Vital signs, 12-lead ECGs, and clinical laboratory tests are presented as descriptive statistics (mean, standard deviation, median, minimum, maximum) for the values measured at each time point and the amount of change from the baseline by dose group for continuous variables. In addition, for test results classified as normal, not clinically significant abnormal (NCS), and clinically significant abnormal (CS), a shift table after administration compared to the baseline is presented. A separate list is presented when there is a change from a normal or a not clinically significant abnormal (NCS) to a clinically significant abnormal (CS). Neurological examination summarizes the frequency of clinically significant abnormalities at each time point, and descriptive statistics according to appropriate classification such as dose group.

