## 14. Analytical and Statistical Considerations

### 14.1. Analysis Populations

1) Demographic information analysis group

Demographic information is analyzed for all subjects (Intention-To-Treat) assigned a randomization number.

2) Safety/tolerability evaluation population

All subjects who have been administered investigational drugs more than once. Analyze according to the type of dose group and treatment group.

3) Pharmacokinetic evaluation population

After completing the clinical study, the subjects who can evaluate the pharmacokinetic results are analyzed. Pharmacokinetic evaluation basically targets subjects with evaluable drug concentrations. If a subject drops out after receiving drug administration, the results obtained from the subject until the time of discontinuation or withdrawal may also be reviewed.

4) Pharmacodynamic evaluation population

After completing the clinical study, the subjects who can evaluate the pharmacodynamic results are analyzed.

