### 14.2. Statistical Analysis Methods

1) Demographic information

For demographic information such as age, height, and weight, descriptive statistics (mean, standard deviation, median, minimum, maximum, etc.) or category frequency and ratio are presented according to the characteristics of the data.

2) Safety and Tolerability Analysis

For safety/tolerability analysis, the abnormal findings observed in safety evaluation lists such as the occurrence pattern of adverse events, vital signs and clinical laboratory results are described, and if necessary, each list is compared according to appropriate classification such as dosing group. Medical history and AEs are coded using the MedDRA (ver. 24.0 or later).

3) Pharmacokinetic Analysis

After calculating pharmacokinetic parameters for each subject, descriptive statistics are summarized by appropriate classification such as dosing group.

To evaluate the pharmacokinetic linearity according to the dose increase, the relationship between  $C_{\max}$ , AUC( $AUC_{\inf}$ ,  $AUC_{\text{last}}$ ) and the administered dose is evaluated through regression analysis, and  $C_{\max}$ , AUC corrected for the administered dose are compared between dosing groups through a parametric or non-parametric statistical test. In addition, parameters such as  $T_{\max}$ ,  $t_{1/2}$ , CL/F can be compared between dosing groups through an appropriate method.

Food effect evaluation is performed by calculating the geometric mean ratio (GMR) of the pharmacokinetic parameters ( $C_{\max}$ , AUC) after a high-fat meal to the fasting and its 90% confidence interval (CI).

4) Exploratory Pharmacodynamic Analysis

After calculating exploratory pharmacodynamic parameters for each subject, descriptive statistics are summarized by appropriate classification such as dosing group.

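### AE tables by dose group set the 120 mg single-dose cohort (two doses, at least 25-32 days) beside cohorts with one dose and 11-15 days

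*Protocol*

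**What the plan says.** Section 12.1.2 fixes the AE summary. It asks for subjects affected and events, for all and for serious events: "Summarize the number of subjects (occurrence rate) and the number of occurrences of adverse events/adverse drug reactions and serious adverse events/adverse drug reactions by dose" and so on, ending with "serious adverse events/adverse drug reactions by dose group and treatment group". Section 14.1 repeats the grouping for the safety population: "Analyze according to the type of dose group and treatment group". Section 10.5 shows what treatment group means, since "the Principal Investigator remains blind to the treatment group (test group or placebo group"; it does not mean fasted or fed.

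Section 14.2 is looser: "if necessary, each list is compared according to appropriate classification such as dosing group". It names no split by period.

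Sections 9.1 and 10.1 make cohort 3 (120 mg) a fixed-sequence, two-period cohort. Every subject is dosed fasted in phase 1 and after a high-fat meal in phase 2, at least 14 days later. Subjects then "conduct the Post Study Visit(PSV) between 12d and 19d from the phase2 dosing date at their convenience". For the single-dose cohorts at 30, 60, 240, 480 and 960 mg there is one dose, and "The subjects who complete whole study conduct the Post Study Visit(PSV) between 12d and 16d at their convenience". In the flow charts, AE monitoring covers days 1 to 7 of both phases plus the post-study visit (PSV) for cohort 3, and one such block plus the PSV for the others.

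**The concern.** Five of the six single-dose groups contribute one administration and one observation window per subject. The third dose level contributes two administrations and roughly twice the observation time. A subject counts as affected if an AE occurs in either period, so the 120 mg row answers a different question from the rows above and below it.

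Safety and tolerability form part of the primary objective, and readers will scan these rows for a trend with dose. Extra exposure at one mid-range level can look like a peak at 120 mg, or can flatten a true rise towards 240-960 mg. An event that occurs only in the fed state would also be read as an effect of the 120 mg dose.

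**Working it through.** **Inputs from the protocol**
- Cohort size: 6 test and 2 placebo (section 9.1). The planned total reproduces: 6 × 8 + 5 × 8 = 48 + 40 = 88.
- Interval between the two cohort 3 doses: at least 14 days.
- PSV: 12d-19d of phase 2 for cohort 3, and 12d-16d for the other single-dose cohorts.
- AE rate: not given. Assumed range 10-30% per period, with within-subject correlation ρ between periods of 0 or 0.3 (also assumed).

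**Follow-up from first dose** (dosing day is 1d)
- Other cohorts: 12 − 1 = 11 to 16 − 1 = 15 days.
- Cohort 3 at the minimum interval: 14 + (12 − 1) = 25 to 14 + (19 − 1) = 32 days.
- Ratio at the earliest PSV: 25/11 = 2.27. Ratio at the latest: 32/15 = 2.13.
- A longer interval between doses lengthens the cohort 3 window. If 12-19 is read as days elapsed since the phase 2 dose, each end moves up by one day.

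**Subject incidence over two periods**

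Let p be the chance of at least one AE in one period. Then

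P(AE in either period) = 2p − [p² + ρp(1 − p)],

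which is 1 − (1 − p)² when ρ = 0.

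| p (one period) | ρ = 0 | ratio | ρ = 0.3 | ratio |
|---|---|---|---|---|
| 10% | 19.0% | 1.90 | 16.3% | 1.63 |
| 20% | 36.0% | 1.80 | 31.2% | 1.56 |
| 30% | 51.0% | 1.70 | 44.7% | 1.49 |

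Example for p = 20%, ρ = 0.3: 0.40 − [0.04 + 0.3 × 0.16] = 0.40 − 0.088 = 0.312.

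**What this means for six active subjects** (p = 20%, ρ = 0, all completing both periods)
- Expected subjects with an AE: 6 × 0.36 = 2.16, against 6 × 0.20 = 1.20.
- Probability that at least 2 of 6 are affected: 0.70, against 0.35.
- Expected events, counting p as the mean number per period: 12 × 0.20 = 2.4, against 6 × 0.20 = 1.2.

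**Can the periods be separated?** Section 5.2.2 expects a half-life of about 36 hours, so 14 days is 336/36 ≈ 9.3 half-lives. On that estimate little drug remains at the second dose, and attribution by period of onset is sensible. Section 13.2 already records the AE onset date, and the time where available.

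**Earliest overlap.** Phase 2 dosing can fall on study day 1 + 14 = 15. An onset window reaching day 15 or 16 could therefore include fed-period events.

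**The case against.** The strongest reply is that assigning AEs to crossover periods and laying out columns is ordinary SAP content, and the SAP is not at hand. Section 14.2 leaves room for other classifications, and neither 12.1.2 nor 14.1 says that the stated grouping is the only one. That is fair, and a SAP could cure the problem. But the protocol is not silent: it names a grouping in two places, and following it produces the unbalanced row.

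Several limits stand:
- The tables are descriptive, with six active subjects per cohort, in a study that section 9.4 calls exploratory. No test is invalidated.
- The protocol labels the group as the food-effect group and often lists it apart from the other single-dose cohorts, so an alert reader is partly warned.
- Vital signs, ECGs, laboratory values and neurological findings are summarised by time point, and cohort 3 time points are defined by phase. The problem lies in the AE incidence and counts, not in every safety output.

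A reader might infer that dose escalation is compromised. The documents do not support this: sections 10.5 and 10.6 base escalation on committee review and graded reactions, not on this summary. A reader might also infer that 120 mg active versus its own placebo is distorted. It is not distorted by duration, because both arms have two periods. Nor does the protocol state that placebo subjects will be pooled across cohorts, so no bias can be charged to that step.

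**Conclusion.** The point holds for comparisons of AE incidence and counts across the single-dose groups. The upward direction does not depend on the assumed rate: including a second dose and its follow-up cannot reduce the number of subjects ever affected or the number of events.

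The size does rest on assumptions. With equal rates in the two periods, all subjects completing both, and ρ between 0 and 0.3, subject incidence at 120 mg is inflated about 1.5 to 1.9 times for per-period rates of 10-30%. It is tempting to say that incidence simply doubles. Expected event counts do double under equal rates, but subject incidence rises by less, and by less still when the same subjects tend to report AEs in both periods. Dropout before phase 2 would shrink the effect further.

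The consequence is a distorted descriptive picture of tolerability by dose, with fed and fasted events mixed at one level. It should be corrected, but it does not undermine the trial.

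**What to change.** Add to section 12.1.2, with a cross-reference in 14.1:
- Each cohort 3 AE is assigned to the period of onset. Phase 1 (fasted) runs from phase 1 dosing to just before phase 2 dosing, and phase 2 (fed) from phase 2 dosing to the PSV.
- The 120 mg fasted and 120 mg fed results are tabulated separately, for active and for placebo. A two-period total may also be shown if labelled as such.
- Comparisons across single-dose groups use only the fasted period of cohort 3, with one common onset window for all cohorts that ends before the phase 2 dose, no later than day 14.

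The cost is one or two extra columns and no new data. Slightly fewer late events enter the cross-dose comparison; they remain in the full tables. Ascertainment will still not match exactly: after day 7, cohort 3 has no scheduled visit until phase 2 admission, while the other cohorts have a PSV at 12d-16d. A footnote should say so. It should also note that the fed period always comes second, so the two columns describe the periods but do not isolate the effect of food.

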### 12.2. Pharmacokinetic Assessments

#### 12.2.1. Pharmacokinetic Endpoints

- Single ascending dose study
  - Primary endpoints:  $AUC_{last}$ ,  $AUC_{inf}$ ,  $C_{max}$ ,  $T_{max}$ ,  $t_{1/2}$ ,  $CL/F$ ,  $V_z/F$ ,  $f_e$ ,  $CL_R$  for KDS2010
  - Secondary endpoints:  $AUC_{last}$ ,  $AUC_{inf}$ ,  $C_{max}$ ,  $T_{max}$ ,  $t_{1/2}$ , metabolic ratio for KDS8170(main metabolite of

KDS2010)

- Multiple ascending dose study
  - Primary endpoints:  $AUC_{\tau}$ ,  $C_{\max,ss}$ ,  $C_{\min,ss}$ ,  $C_{av,ss}$ ,  $T_{\max,ss}$ ,  $t_{1/2}$ , PTF,  $CL_{ss}/F$ ,  $V_{d,ss}/F$ ,  $f_e$ ,  $CL_R$ , accumulation ratio (Ra) for KDS2010
  - Secondary endpoints:  $AUC_{\tau}$ ,  $C_{\max,ss}$ ,  $C_{\min,ss}$ ,  $C_{av,ss}$ ,  $T_{\max,ss}$ ,  $t_{1/2}$ , PTF, accumulation ratio (Ra), metabolic ratio for KDS8170(main metabolite of KDS2010)

### 12.2.2. Pharmacokinetic Analysis

In pharmacokinetic analysis, blood sampling/urine collection time is analyzed using the actual blood sampling/urine collection time for each subject. If the measured concentration is below the lower limit of quantification(LLOQ), or no actual blood sampling has been performed (not applicable), or the sample is missing (missing data), it is written as "LLOQ", "NA", or "MD" in the blood drug concentration data, respectively. If the blood concentration is less than the lower limit of quantification before  $T_{\max}$ , it is regarded as 0, and if the blood concentration observed near the terminal after  $T_{\max}$  is less than the lower limit of quantification, it is regarded as a missing data. The obtained data are used to calculate pharmacokinetic parameters by a noncompartmental method using WinNonlin® (Certara, CA, USA).

### 12.3. Pharmacodynamic Assessments

#### 12.3.1. Pharmacodynamic Endpoints

- MAO-B activity

#### 12.3.2. Pharmacodynamic Analysis

Analyze the change and rate of change of MAO-B activity compared to the baseline.

## 13. Reporting of Adverse Events

### 13.1. Definition of Safety Terms

#### 13.1.1. Adverse Event (AE)

An adverse event (AE) refers to all harmful and unintended signs(including an abnormal laboratory finding), symptom or disease that occur in subjects who have administered the investigational drug, and it does not necessarily have to have a causal relationship with the investigational drug.

#### 13.1.2. Adverse Drug Reaction (ADR)

An adverse drug reaction (ADR) refers to all noxious and unintended responses to the investigational drug related to any dose. The phrase “responses to the investigational drug” means that a causal relationship between investigational drug and an adverse event is at least a reasonable possibility, i.e., the relationship cannot be ruled out.

#### 13.1.3. Serious Adverse Event/Adverse Drug Reaction (AE/ADR)

Any AE/ADR occurring at any dose of the investigational drug that results in any of the following outcomes:

- 1) Results in death or life-threatening

- 2) Requires inpatient hospitalization or prolongation of existing hospitalization
- 3) Results in persistent or significant disability/incapacity
- 4) Results in congenital anomaly/birth defect
- 5) In addition to cases 1) to 4), cases where drug dependence or abuse occurs or other medically important circumstances such as occurrence of blood diseases

If a situation that is medically considered to have a significant impact on the subject's safety and health condition other than those listed above occurs, it is decided whether or not to be regarded as a serious adverse event according to the medical judgment of the investigator and related experts. And take appropriate action accordingly. However, the following subjects are not considered SAEs.

- Hospitalization for pre-planned treatment/surgical procedures prior to participation in the clinical study, or hospitalization selected by the subject for pre-existing concomitant diseases that did not worsen during the study period, and extension of hospitalization period accordingly (Hospitalization for a rehabilitation institution, nursing institution, nursing home, or temporary care that continued before administration of the investigational drug, and hospitalization for laboratory abnormalities, when the subject lives far from the hospital or there is no caregiver at home, etc.)
- Discharge within 24 hours of hospitalization (Emergency room visits that do not result in hospitalization)

#### 13.1.4. Suspected Unexpected Serious Adverse Reaction (SUSAR)

Suspected Unexpected Serious Adverse Reaction (SUSAR) is suspected of being drug-related, unexpected, and serious adverse drug reaction.

### 13.2. Recording and Reporting of Adverse Events

- 1) Adverse events must be specified in source document and case report form. In source document, the symptoms or signs are freely indicated as subject expression or opinion of principal investigator or clinical study doctor. However, case report form based on source document is recorded using MedDRA (version 24.0 or the latest available version) as much as possible and record as LLT (Lowest Level Term), and encode according to SOC and PT during analysis.
- 2) The symptoms and signs from screening to drug administration are recorded in "medical history" of CRF.
- 3) In the case report form, the symptoms and signs, the date and time of onset (if possible), the action taken, the outcome, the severity of the adverse events and the causal relationship with the investigational drug should be described. The clinical trial coordinator may write the case report form for adverse events, but the final review and confirmation must be done by the principal investigator. In addition, the content, start, termination, total duration, and action taken of the adverse events must be written in a case report form based on the source document. The degree of occurrence, result, causal relationship, and reporting method can be directly recorded in the case report form by the principal investigator or the clinical study doctor, and in this case, the content of the case report form becomes the source data.
- 4) In case the symptoms and signs of an adverse event persist, that is, if the outcome of the adverse event is 'continuation of adverse event', even if observation of the subject is terminated at the discretion of the principal investigator or the clinical study doctor, the records of the voluntary reports of subject should be kept in the source document. If necessary, the case report form may be rewritten including this.
- 5) Information to be recorded in the case report form
  - ① Symptom and sign
  - ② Date and time of onset (if available)
  - ③ Date and time of end (if available)
  - ④ Outcome
  - ⑤ Severity

- ⑥ Causal relationship with the investigational drug
- ⑦ Action taken
- ⑧ SAE or not
- ⑨ Progress

